## Abstract

**Background:**

Suicidality, ranging from passive suicidal thoughts to suicide attempt, is common in major depressive disorder (MDD). However, relatively little is known about patient, illness and treatment characteristics in those with co-occurring MDD and suicidality, including the timing of and factors associated with the offset, continuation or reemergence of suicidality. Here, we present the background, rationale, design and hypotheses of the Patient Characteristics, Validity of Clinical Diagnoses and Outcomes Associated with Suicidality in Inpatients with Symptoms of Depression (OASIS-D) study, an investigator-initiated, observational study, funded by Janssen-Cilag GmbH.

**Methods/Results:**

OASIS-D is an eight-site, six-month, cohort study of patients aged 18-75 hospitalized with MDD. Divided into three sub-studies and patient populations (PPs), OASIS-D will (i) systematically characterize approximately 4500 consecutively hospitalized patients with any form of unipolar depressive episode (PP1), (ii) evaluate the validity of the clinical diagnosis of moderate or severe unipolar depressive episode with the Mini-International Neuropsychiatric Interview (M.I.N.I.) and present suicidality (at least passive suicidal thoughts) present ≥ 48 h after admission with the Sheehan-Suicide Tracking Scale (S-STS), assessing also predictors of the diagnostic concordance/discordance of MDD in around 500 inpatients (PP2), and (iii) characterize and prospectively follow for 6 months 315 inpatients with a research-verified moderate or severe unipolar depressive episode and at least passive suicidal thoughts ≥ 48 h after admission, evaluating treatment and illness/response patterns at baseline, hospital discharge, 3 and 6 months. Exploratory objectives will describe the association between the number of days with suicidality and utilization of outpatient and inpatient care services, and structured assessments of factors influencing the risk of self-injurious behavior without suicidal intent, and of continuous, intermittent or remitted suicidality during the 6-month observation period.

**Conclusion:**

Despite their frequency and clinical relevance, relatively little is known about patient and treatment characteristics of individuals with MDD and suicidality, including factors moderating and mediating the outcome of both MDD and suicidality. Results of the OASIS-D study are hoped to improve the understanding of the frequency, correlates and 6-month naturalistic treatment and outcome trajectories of different levels of suicidality in hospitalized adults with MDD and suicidality.

**Trial registration:**

NCT04404309 [ClinicalTrials.gov]

## Background

Major depressive disorder (MDD) is among the most common mental disorders worldwide and has been increasing in recent decades [1]. The lifetime prevalence of MDD exceeds 10% [2, 3]. MDD criteria include depressed mood, diminished interest or pleasure, weight or appetite increase or decrease, insomnia or hypersomnia, psychomotor agitation or retardation, fatigue or loss of energy, feelings of worthlessness or inappropriate guilt, diminished ability to think or concentrate, or indecisiveness, and recurrent thoughts of death or recurrent suicidal ideation [4].

Patients with MDD are more frequently female, older [5, 6] and most often cared for in primary care settings [7, 8], where most antidepressants, mostly selective serotonin reuptake inhibitors (SSRIs) [9, 10] are prescribed, with escalation to secondary or inpatient care in cases of more severe acute or dangerous clinical scenarios. MDD requiring hospitalization may follow those demographics but has also been associated with treatment-resistant depression, occurring in approx. 20% of people with MDD [11], presence of passive or active suicidal ideation [12, 13], and lifetime history of a suicide attempt, which is present in approximately 20% of people with MDD [14].

Suicide is a significant public health problem. The World Health Organization (WHO) has reported more than 700,000 deaths per year (1/100) worldwide due to suicide in 2019. Among 15–29-year olds, suicide is the fourth leading cause of death, and 58% of suicides occurred before the age of 50 years [15]. Suicide attempts are generally preceded by various forms of suicidal ideation. Often, national surveys do not measure passive suicidal ideation, but only active suicidal ideation [16–18]. One possible reason for this is that suicidality has historically been thought to progress along a continuum, from passive suicidal ideation (i.e., thoughts about death or a desire for death in general), to active suicidal ideation (i.e., thoughts of killing oneself) to suicidal plans, to suicidal behavior [19, 20]. However, recent studies suggest that there is no such continuum and that the association between passive suicidality and suicidal behavior and between active suicidality and suicidal behavior is comparable [12, 13, 19]. Therefore, studies must include passive suicidal ideation.

MDD is one of the disorders most strongly associated with suicidality [21]. For example, in patients with MDD, at least passive suicidality is present in about 50% [22], lifetime prevalence of suicide attempts is 31% [23], and lifetime prevalence of completed suicide is up to 10% [24–26], more than 20 times higher than in the general population [27]. In fact, in a meta-analysis, next to previous suicidal behaviors, severe depressive symptoms was the only other factor that was significantly associated with suicidal ideation, suicide attempt as well as death by suicide [28]. This high co-occurrence of depressed mood with suicidality justifies the inclusion of suicidal thoughts and actions as a criterion for depressive disorder in the Classification of Mental and Behavioural Disorders (ICD-10) [29] and Diagnostic and Statistical Manual of Mental Disorders (DSM-5) [4].

Few studies have examined features that are correlated with depression with and without suicidality, including worthlessness, guilt, despair, depressive and manic symptoms, inner restlessness and agitation, sleep disturbances, previous suicidal behavior, hopelessness, rumination, social withdrawal, lack of activity, crying, self-injurious behavior, feelings of loss of control, experiences of derealization, and course of depression [30–34]. Furthermore, individual studies have identified relatively few factors that can influence the course of depression with suicidality, e.g. severity of depression, comorbid disorders, including anxiety, hopelessness, anger, misuse of alcohol and drugs, and personality disorders [34–37].

A meta-analysis showed that among general practitioners, the rate of correctly confirmed MDD diagnoses by psychiatric interview was 47.3% [38], with an increased likelihood of suboptimal medication management in the absence of MDD. However, the fact that general practitioners do not have specialist psychiatric training may explain the low rate. To what degree psychiatric care practitioners and trainees who often make the first diagnoses during the evaluation in the emergency room prior to hospitalization have a higher concordance rate between the clinical and research interview-derived MDD diagnosis requires further study. Although isolated reports have found associations between younger patient age [39], and comorbid personality disorders [40, 41] with discordance between a clinical and a gold-standard research diagnosis of MDD, more extensive research is needed to identify which patient demographic, illness or treatment factors are associated with a discordant MDD diagnosis.

Moreover, while clinical correlates of suicidal thoughts and suicidal behaviors have been researched extensively in MDD, the pattern of remission, recovery and recurrence of suicidal thinking and suicide attempts after an inpatient admission for MDD has received little attention. Based on the association between the severity of MDD and prior suicidality, other psychiatric comorbidities and indicators of disease severity, it is reasonable to assume that the following characteristics may also predict persistence, recurrence and severity of suicidality. Such factors include presence [28, 36, 42, 43] and duration [44] of depressive symptoms, anxiety symptoms [28, 36, 45], anger and hostility [43], comorbid borderline personality disorder [35, 46] and substance use disorder [28], suicidality at the index episode [28, 36, 42, 47], and impaired quality of life [48, 49].

For diagnosed MDD, guidelines recommend psychotherapeutic interventions for the treatment of MDD, with cognitive-behavioral therapy (CBT) having the strongest evidence of effectiveness. Moreover, antidepressants are recommended for moderate to severe MDD. With regard to suicide risk in MDD, suicidality should be continuously assessed during treatment [50–53]. In cases of acute suicidality, the management plan should be based on the person's ability to consent to a no-harm agreement and on individual risk and environmental factors [51, 52]. Thereby, crisis intervention, such as hospitalization [53] and/or suicide-focused psychotherapy should be offered, and an emergency plan be developed with the patient [52]. In addition, antidepressant treatment is recommended for depressed patients with suicidality [51–53]. However, antidepressants are not recommended for suicidal crises because it takes up to 4 weeks for the antidepressant to take full effect [52, 54]. Benzodiazepines are recommended for short-term treatment to reduce, among other symptom domains, insomnia and agitation, which is also associated with a positive effect on acute suicidality [52, 55, 56], although their cost–benefit ratio is debated [57–60]. In psychiatric emergencies, especially in cases of acute suicidality, esketamine can be offered intranasally or ketamine intravenously in addition to an antidepressant [52, 61]. Moreover, intranasal esketamine has also shown efficacy for treatment-resistant depression, and is recommended by guidelines for this indication [52, 62–64]. Lithium can be offered when facing chronic suicidality [52, 65, 66]. As a last resort, electroconvulsive therapy can be offered in addition to psychotherapeutic crisis intervention in cases of acute suicidality [52, 55]. Understanding the factors that influence the trajectory of suicidal ideation and attempts in patients with MDD is crucial for enhancing the timing, sequencing and selection of targeted treatment strategies. Factors influencing the management plan include the severity of depressive symptoms [28, 36, 42, 43], comorbid disorders such as anxiety [28, 36, 43, 45] and personality disorders [35, 46], personality traits such as anger [43], and degree of quality of life impairment [48, 49]. Furthermore, the degree to which previous suicidal ideation and attempts can predict future suicidal ideation and attempts has been discussed [67–69]. However, a recent study did not support this connection, indicating that further research is required for verification or for a more precise delineation of patient subgroups who are at particularly high risk for recurrence or chronicity of suicidal thought and/or behaviors [70].

However, there remains a large information gap to better predict disease trajectories in patients with MDD and suicidality. Moreover, no standard of care treatments have been established and there is a need to explore new treatment options. The naturalistic Patient Characteristics, Validity of Clinical Diagnoses and Outcomes Associated with Suicidality in Inpatients with Symptoms of Depression (OASIS-D) study aims to improve the understanding of the frequency, correlates and 6-month naturalistic treatment and outcome trajectories of different levels of suicidality in hospitalized adults with MDD and suicidality. Such additional information can be used to guide clinicians toward focusing on specific patient subgroups at risk for more severe, chronic or dangerous suicidality and, possibly, devise a clinical standard of care for future comparator studies of novel agents aimed at reducing suicidality and its serious consequences in patients with MDD.

### Trial design

OASIS-D has three different parts. Part one consists of a cross-sectional epidemiological chart review study in which basic historical and clinical characteristics, including past and current presence of suicidality, will be recorded in all consecutively hospitalized patients with MDD (patient population 1 (PP1)). Part two includes a consented subgroup of PP1 with suicidality that even ≥ 48 h post admission still presents with suicidality (eliminating transient, brief suicidality in response to an acute internal or psychosocial stressor) and that consents to undergo in-depth assessments of their past and present psychiatric history, psychiatric diagnoses and psychopathology, including suicidality (PP2). Part 3 includes a subgroup of PP2 whose MDD diagnosis and ongoing suicidality have been confirmed with research interviews and who are followed naturalistically for 6-months, reflecting usual care of adults with MDD and suicidality. Data collection will occur at inpatient admission (T0, epidemiological PP 1), at baseline in patients with ongoing suicidality, i.e. at least 48 h after T0 (T1; PP2 as a subgroup of PP1), and in PP3 (subgroup of PP2) at T1 (more detailed baseline assessments), discharge (T2), 3 months after T1 (T3) and 6 months after T1 (T4) (see Fig. 1). Due to the variability of hospital discharge (T2), the T2 assessment may occur after T3 (3 months) or concurrently with T4 (6 months).

**Fig. 1 Fig1:**
[figure not shown]
Study design of OASIS-D

### Objectives

The primary objective 1 of PP1 is to systematically characterize patients consecutively admitted to a psychiatric inpatient unit with any current form of clinically diagnosed depressive episode that is part of MDD, and not of bipolar disorder.

The primary objective 2 of PP2 is to evaluate the validity of the clinical diagnosis of moderate or severe unipolar depressive in inpatients using a gold-standard research interview, and the predictors of the diagnostic concordance/discordance.

The primary objective 3 of PP3 is to conduct a 6-month, prospective, naturalistic follow-up study in a subgroup of PP2 that has verified moderate to severe MDD and ongoing suicidality using structured assessments of the duration and severity of suicidality, the frequency of recurrence of suicidality as well as any significant moderators and mediators.

### Primary inclusion criteria

Inclusion criteria for PP1 are (i) male and female patients; (ii) aged between 18 and 75 years; (iii) admitted to a psychiatric inpatient unit, and (iv) having an ICD-10-based chart diagnosis of single depressive episode (F32) or recurrent depressive episode (F33).

Inclusion criteria for PP2 (originating from PP1) are (i) male and female patients; (ii) aged between 18 and 75 years; (iii) admitted to a psychiatric inpatient unit; (iv) having an ICD-10-based *clinical* diagnosis of a single or recurrent depressive episode of *at least moderate severity*, including single depressive episode, moderate episode (F32.1), single depressive episode, severe episode without psychotic symptoms (F32.2), single depressive episode, severe episode with psychotic symptoms (F32.3), recurrent depressive episode, currently moderate episode (F33.1), recurrent depressive episode, currently severe episode without psychotic symptoms (F33.2), and recurrent depressive episode, currently severe episode with psychotic symptoms (F33.3); (v) *clinically* diagnosed suicidality that persists for ≥ 48 h after inpatient admission; and (vi) sufficient German language skills to understand the purpose and procedures of the study and cooperate with the study procedures; and (vii) providing written informed consent to participate in the study.

Inclusion criteria for PP3 (originating from PP2) are (i) male and female patients; (ii) aged between 18 and 75 years; (iii) admitted to a psychiatric inpatient unit; (iv) having an ICD-10-based *research* diagnosis according to the Mini-International Neuropsychiatric Interview (M.I.N.I.) [71] of a single or recurrent depressive episode of *at least moderate severity* (for details, see PP2 above); (v) *research interview-based* suicidality with a score ≥ 1 on item 2 (passive suicidality) OR item 3 (active suicidality) using the Sheehan–Suicidality Tracking Scale (S-STS) [21]; (vi) written informed consent to participate in the study.

### Exclusion criteria

Exclusion criteria for PP1 are (i) psychiatric inpatients younger than 18 years and older than 75 years; (ii) no clinical diagnosis of a unipolar depressive episode; (iii) depressive episode in the context of bipolar disorder.

Exclusion criteria for PP2 and PP3 are (i) psychiatric inpatients younger than 18 years and older than 75 years; (ii) depression secondary to a physical illness, such as hypothyroidism or vitamin B12 deficiency, or substance use; (iii) severe physical illness symptoms that preclude participation in the study; (vi) unable to understand the study procedures; (v) unable to give informed consent; (vi) unable to give consent due to (limited) legal capacity.

### Aims and hypotheses

The primary aim in PP1 is to systematically characterize patient, illness, and treatment characteristics of consecutively admitted patients with a clinical diagnosis of a single or recurrent unipolar depressive episode.

#### Hypothesis 1

We hypothesize that MDD at inpatient admission is characterized by (i) most frequent referral by a primary care physician, (ii) female patient predominance of about 60% [5, 6], (iii) older patients aged approx. 45 years [5, 6], (iv) admission due to psychiatric emergency in approx. 25% of the sample, (v) occurrence of treatment-resistant depression in approx. 20% of the sample [11], (vi) occurrence of at least passive suicidal ideation in at least 50% of the sample [6, 72], (vii) lifetime history of a suicide attempt in approx. 20% of the sample [14], and (viii) preponderance of medication treatment with selective serotonin reuptake inhibitors (SSRIs) [9, 10].

#### Hypothesis 2

The primary aim in PP2 is to test the validity of the clinical diagnosis of at least moderately severe MDD in patients with clinically documented suicidality using the M.I.N.I. and compare predictors (diagnosis, demographic and illness characteristics, treatment) between patient groups with concordant and discordant clinical and research diagnosis.

Hypothesis 2A: We hypothesize that in < 50% of patients the clinical diagnosis will not be confirmed by the structured research diagnosis [38].

Hypothesis 2B: We hypothesize that the patient group with unvalidated vs validated clinical diagnosis of at least moderately severe MDD by the research interview compared will be associated with (i) younger age (less historical information and more dynamic emergence of (co)morbidities) [39], (ii) female sex (possible diagnostic bias), (iii) lower number of previous depressive episodes (less historical validation), (iv) lower number of index admission in the context of a psychiatric emergency (less historical validation), (v) higher number of comorbid personality disorders (more diagnostic overlap) [40, 41], and (vi) lower suicidal severity (less severe psychiatric condition).

#### Hypothesis 3

The primary aim of PP3 is a 6-month structured recording of the duration and frequency persistence and recurrence of suicidality and its correlates in 315 patients diagnosed with at least moderately severe MDD by the M.I.N.I. and with confirmed presence of at least passive suicidal ideas by the S-STS ≥ 48 h after inpatient admission.

Hypothesis 3A: We hypothesize that the time to remission of suicidal symptoms after the baseline is a major determinant of shorter overall duration of passive or active suicidal ideation (PASI) during the entire 6-month observation period.

Hypothesis 3B: We hypothesize that the rate of remission of suicidal symptoms after baseline is a major determinant of lower recurrence of PASI during the 6-month observation period.

Hypothesis 3C and 3D: We hypothesize that a longer total duration of PASI (Hypothesis 3C) and a greater risk of recurrence of PASI after complete remission (Hypothesis 3D) during the 6-month observational phase is associated with the following factors at time T0 (i.e., “moderators”): greater severity of (i) depressive symptoms [28, 36, 42, 43], (ii) manic symptoms (below the threshold of (hypo)mania as part of MDD), (iii) anxiety symptoms [28, 36, 45], (iv) anger and hostility [43], (v) quality of life impairment [48, 49], (vi) global symptoms of illness and (vii) suicidality [28, 36, 42, 47], (viii) higher number of lifetime depressive episodes, (viii) index admission as part of a psychiatric emergency, (ix) longer duration of current depressive episode [44], (x) higher non-adherence to pharmacological and non-pharmacological treatments, (xi) comorbid borderline personality disorder [35, 46], and (xii) comorbid substance use diagnosis [28].

Exploratory study aim 1 of PP3 is to describe the association between PASI and suicide attempts (S-STS item 14) as well as with the utilization of outpatient and inpatient care services during the 6-month observation period.

Exploratory hypothesis 1A, 1B and 1C: We hypothesize that a higher number of days with PASI (exploratory hypothesis 1A), a higher number of days with active suicidal ideation (exploratory hypothesis 1B) and a higher number of suicide attempts (exploratory hypothesis 1C) during the 6-month observation period are significantly associated with a higher number of (i) outpatient appointments, (ii) emergency department visits, (iii) inpatient hospitalizations, (iv) hospitalizations as part of psychiatric emergencies, (v) psychiatric hospital bed days, and (vi) suicide-related hospital bed days.

Exploratory study aim 2 of PP3 is to assess risk factors for different levels of active suicidality, consisting of active suicidal ideation (S-STS item 3), active suicidality with preparatory action (S-STS 12), self-injurious behavior without suicidal intent (S-STS item 13), or suicide attempts (S-STS item 14).

Exploratory study hypothesis 2: Active suicidality as defined above is associated with (i) slower rate of remission of suicidal symptoms after baseline, greater baseline severity of (ii) depressive symptoms, (iii) manic symptoms (below the threshold of (hypo)mania as part of MDD), (iv) anxiety symptoms, (v) anger and hostility, (vi) quality of life impairment (vii) global illness symptoms, and (viii) suicidality, (ix) higher number of lifetime depressive episodes, (x) duration of current depressive episode, (xi) index admission as part of psychiatric emergencies, (xii) higher non-adherence to pharmacological and non-pharmacological treatments, (xiii) comorbid borderline personality disorder, and (xiv) comorbid substance use diagnosis.

### Assessments and timeline

In PP1, sociodemographic, family, illness, and treatment-related data are collected to characterize patients with MDD at the time of inpatient admission (T0), i.e., age (coded in 5 year intervals), sex, ICD-10 F-diagnosis, current and lifetime suicidality, psychiatric emergencies, current and previous treatments, medication resistance, and nonadherence.

In PP2, sociodemographic, illness and treatment data (i.e., sex, Body-Mass-Index (BMI), family psychiatric disorders, education/ work, pathways to admission, F-diagnosis of ICD-10, illness duration, number of episodes, current and lifetime suicidality, psychiatric emergency, current and previous treatment, medication treatment-resistance and non-adherence, substance use) are collected at ≥ 48 h after inpatient admission (T1). M.I.N.I. will be used as an interview to determine the research diagnosis of at least moderately severe MDD, and S-STS will be used to assess suicidality.

In PP3, assessments are performed at time points ≥ 48 h after admission (T1), inpatient discharge (T2), 3 months after T1 (T3, by telephone), and 6 months after T1 (T3). The following investigator interviews and rating scales will be performed: For suicidality the S-STS, for depression the Montgomery-Asberg Depression Rating Scale (MADRS) [73], for global improvement change the Clinical Global Impression-Change (CGI-C) [74], for global severity of illness the Clinical Global Impression-Severity (CGI-S) [75], for imminent suicide risk the Clinical Global Impression of Imminent Suicide Risk (CGI-I), and for resolution of suicide risk the Clinical Global Impression of resolution of Suicide Risk (CGI-SR-R), for mania the Young Mania Rating Scale (YMRS) [76], for personal and social performance the Personal and Social Performance Scale (PSP) [77], for service use the Service Use and Resource Form (SURF) [78], for borderline disorder the ICD-10 borderline criteria (Table 1). Additionally, information obtained from patients regarding psychotropic medications (reason of initiation, discontinuation, switching, effectiveness, safety), electroconvulsive therapy, substance use, and presence of specific psychiatric emergency as reason for hospitalization. Furthermore, the following self-rating questionnaires will be obtained from the patients: Quick Inventory of Depressive Symptomatology-Self Report (QIDS-S) [79], Beck Depression Inventory-II (BDI-II) [80], Beck Anxiety Inventory (BAI) [81], Quality of Life in Depression Scale (QLDS) [82], European Quality of Life Group, 5-Dimension, 5-Level (EQ-5-DL) [83], 36-item Short-Form Health Survey (SF-36) [84], Work Productivity and Activity Impairment (WPAI) [85], Patient Health Questionnaire 9-item (PHQ-9) [86], Beck Hopelessness Scale (BHS) [87], Munich Chronotype Questionnaire (MCTQ) [88], State -Trait Anger Expression Inventory (STAXI) [89], Aggression Questionnaire-Buss Perry (AF-BP) [90]) (Table 1).

**Table 1 Tab1:** Assessments and timeline

	**T0** **(Inpatient admission)**	**T1** **(≥ 48 h after T0)**	**T2 (Inpatient discharge)**	**T3** **(Month 3 after the 1st examination day of T1 (by telephone unless still hospitalized), if ≥ 2-week interval to T2)**	**T4** **(Month 6 after the 1st examination day of T1, if ≥ 2-week interval from T2)**
**Patient population 1 (data from routine clinical practice + clustering of data into 5-year age intervals with % data on each)**					
Age (coded in 5-year intervals)	+				
Sex	+				
Referral context	+				
ICD-10 F-Diagnosis	+				
Suicidality (current, lifetime)	+				
Psychiatric emergency	+				
Current and previous treatment (medication, psychotherapy, inpatient, electroconvulsive therapy)	+				
Treatment-resistant depression	+				
Medication nonadherence	+				

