**Patient population 3 (M.I.N.I. + S-STS validated)**					
*Psychopathology, suicidality, comorbidity, stressors*					
Montgomery-Asberg Depression Rating Scale (MADRS)		+	+	+	+
Sheehan Suicidality Tracking Scale (S-STS)			+	+	+
Clinical Global Impression—Change (CGI-C)		+	+	+	+
Clinical Global Impression—Severity (CGI-S)		+	+	+	+
Clinical Global Impression of Imminent Suicide Risk (CGI-SR-I)		+	+	+	+
Clinical Global Impression of resolution of Suicide Risk (CGI-SR-R)		+	+	+	+
Mini-International Neuropsychiatric Interview (M.I.N.I.)					+
ICD-10: Borderline criteria checklist		+			
Young Mania Rating Scale (YMRS)		+	+	+	+
Personal and Social Performance Scale (PSP)		+	+	+	+
Previous and current substance use		+	+	+	+
Psychiatric emergency (since last visit, current)			+	+	+
*Self-ratings*					
Quick Inventory of Depressive Symptomatology-Self Report [QIDS-S]^38^		+	+		+
Beck Depression Inventory—II (BDI-II)		+	+		+
Beck Anxiety Inventory (BAI)		+	+		+
Quality of Life in Depression Scale (QLDS)		+	+		+
European Quality of Life Group, 5-Dimension, 5-Level (EQ-5-DL)		+	+		+
36-item Short-Form Health Survey (SF-36)		+	+		+
Work Productivity and Activity Impairment (WPAI)		+	+		+
Patient Health Questionnaire 9-item (PHQ-9)		+	+		+
Beck Hopelessness Scale (BHS)		+	+		+
Munich Chronotype Questionnaire (MCTQ)		+	+		+
State -Trait Anger Expression Inventory (STAXI)		+	+		+
Aggression Questionnaire—Buss Perry (AF-BP)		+	+		+
*Utilization of health services*					
Service Use and Resource Form (SURF)		+		+	+
Documentation of clinical routine and treatment (both outpatient and inpatient) - Medication (including reason for initiation, discontinuation and switching, effectiveness and safety - Electroconvulsive therapy		+	+	+	+
*Physical examination and side effects*					
Body Mass Index (BMI)		+	+		+
Adverse side effect of medication		+	+	+	+
*Adherence*					
Questionnaire for recording adherence		+	+	+	+

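### The 2-week rule for T3 and T4 in Table 1 drops the SURF (and at T4 the M.I.N.I.) for patients discharged near month 3 or month 6, because T2 collects neither, and it does not fit the Trial design text

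*Protocol article*

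**What the plan says.** All references are to the protocol article.

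- **Visit conditions (Assessments and timeline, Table 1 column headings).** T3 is held "by telephone unless still hospitalized), if ≥ 2-week interval to T2". T4 is held at "Month 6 after the 1st examination day of T1, if ≥ 2-week interval from T2".
- **Item grid (Table 1, patient population 3).** The row "Service Use and Resource Form (SURF)" is marked at T1, T3 and T4. The row "Mini-International Neuropsychiatric Interview (M.I.N.I.)" is marked at T4 only; the baseline interview is listed under patient population 2. The row "Documentation of clinical routine and treatment (both outpatient and inpatient)" is marked at T1, T2, T3 and T4.
- **Trial design.** Because discharge varies, "the T2 assessment may occur after T3 (3 months) or concurrently with T4 (6 months)."
- **Use of the data (Aims and hypotheses).** Exploratory aim 1 concerns "utilization of outpatient and inpatient care services during the 6-month observation period". Its outcomes include outpatient appointments, emergency department visits and inpatient hospitalizations, and also "hospitalizations as part of psychiatric emergencies, (v) psychiatric hospital bed days, and (vi) suicide-related hospital bed days".
- **Discharge timing (Sample size and statistical analyses).** The plan acknowledges that the time of T2 is related to the outcome, and for that reason adjusts for the T1 to T2 interval in the comparison of faster and slower remitters.

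**The concern.** A rule that skips a follow-up visit close to discharge is sensible if the discharge visit collects the same items. Here it does so for everything except the SURF and the follow-up M.I.N.I. A site that follows the grid literally has no instruction to complete either one for a patient whose discharge falls in the window.

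The SURF is the instrument named for service use, so the gap falls on exploratory aim 1. Whether a form is missing depends on when the patient leaves hospital. Length of stay is related to outcome by the plan's own account, and it also contributes to the bed-day outcomes. A patient who misses T3 under the rule and then drops out has no SURF after baseline.

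There is also an inconsistency. The Trial design section allows T2 and T4 to coincide, while the Table 1 heading holds T4 only when it is at least 2 weeks from T2. With eight sites, some may run a combined visit with the T4 items and others a T2 visit alone.

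**Working it through.** **1. Which items the rule loses.** An item is lost when it is marked at the skipped visit and blank at T2.

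| PP3 item in Table 1 | T1 | T2 | T3 | T4 | Lost if T3 skipped | Lost if T4 skipped |
|---|---|---|---|---|---|---|
| S-STS | (under PP2) | + | + | + | no | no |
| MADRS, CGI scales, YMRS, PSP, substance use | + | + | + | + | no | no |
| Psychiatric emergency since last visit | | + | + | + | no | no |
| Self-ratings, BMI | + | + | | + | no | no |
| Treatment documentation, side effects, adherence | + | + | + | + | no | no |
| SURF | + | | + | + | **yes** | **yes** |
| M.I.N.I. | (under PP2) | | | + | no | **yes** |

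The loss is therefore confined to one form at T3 and two at T4.

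**2. What happens by discharge date.**

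- Discharge less than 2 weeks before or after month 3: no T3, so no SURF until T4.
- Discharge less than 2 weeks before month 6: no T4, so no T4 SURF and no M.I.N.I. The last contact is T2, up to 2 weeks short of 6 months.
- Discharge at month 6 or less than 2 weeks after it: the 6 months are covered, but no T4 is held under the heading, so the SURF and M.I.N.I. are again missing unless the visits are merged.
- Any other discharge date: T3 and T4 are both held.

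**3. The plan's own sample size.** 315 × (1 − 0.34) = 207.9, which reproduces the stated 208 with month-6 data. That figure and the minimum of 200 (10 patients × about 20 variables) concern the suicidality regressions. Their scale, the S-STS, is collected at T2, so the gap does not reduce them.

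**4. How many patients might be affected.** The document gives no length of stay. As an assumption, let the stay counted from T1 be lognormal with median m of 35 to 63 days (5 to 9 weeks) and log-SD s of 0.5 to 0.7. Take month 3 as day 91 and month 6 as day 183. An interval under 14 days is at most 13 whole days, so with a half-day allowance the windows are 91 ± 13.5 = 77.5 to 104.5 days and 183 ± 13.5 = 169.5 to 196.5 days. With Φ the standard normal distribution function,

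P(a to b) = Φ((ln b − ln m)/s) − Φ((ln a − ln m)/s).

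| Window | m, s | Calculation | P | Of 315 |
|---|---|---|---|---|
| Month 3, lowest | 35, 0.5 | Φ(2.188) − Φ(1.590) = 0.9857 − 0.9441 | 0.042 | 13 |
| Month 3, highest | 63, 0.5 | Φ(1.012) − Φ(0.414) = 0.8443 − 0.6607 | 0.184 | 58 |
| Month 6, lowest | 35, 0.5 | Φ(3.451) − Φ(3.155) = 0.9997 − 0.9992 | 0.0005 | 0 |
| Month 6, highest | 63, 0.7 | Φ(1.625) − Φ(1.414) = 0.9479 − 0.9213 | 0.027 | 8 |

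The month-3 window includes patients still in hospital on day 91. At s = 0.5 they make up about 33% (m = 35) to 41% (m = 63) of that window. A site may not know on day 91 that discharge is less than 2 weeks away, and may hold T3 anyway, so the month-3 counts are on the high side.

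**The case against.** The strongest reply is that the article never says T2 replaces a skipped visit. The Trial design sentence about T2 coinciding with T4 can be read as one combined visit at which the T4 items are collected, and rules for merging visits may sit in the full protocol. This stands in part: the loss follows from a literal reading of the grid, not from a stated intention. But the article itself prints both the condition and the grid, and the heading and the Trial design sentence do not agree, so asking for them to be reconciled is fair.

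A reader might infer that the rule strips service-use data from the longest-stay or heaviest users of care. The document does not support that. Only the month-6 window concerns very long stays. The month-3 window catches discharges at about 2.5 to 3.5 months, and patients who stay longer still have T3 in hospital. Those who miss T3 are still due a SURF at T4, and the article gives no look-back period that would show the T4 form fails to cover the gap. In both windows the patient may have been an inpatient for most of the preceding interval. Index-stay bed days then follow largely from the admission and discharge dates, and treatment documentation and psychiatric emergencies are recorded at T2.

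A reader might also multiply the month-3 counts by the 34% attrition to count patients with no SURF after baseline: 0.34 × 13 to 0.34 × 58, or about 4 to 20. I would not rely on that. The plan describes the higher dropout as arising between discharge and the 6-month follow-up, and this group has a shorter period at risk than patients discharged earlier.

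Finally, no stated hypothesis uses the T4 M.I.N.I., and the analyses are declared hypothesis-generating. That limits the weight of the point.

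**Conclusion.** The point holds in a limited form. As printed, Table 1 loses the T3 SURF for patients discharged near month 3, and the T4 SURF and M.I.N.I. for those discharged near month 6, through a rule tied to discharge timing that the plan itself treats as related to outcome. The Trial design section points to a different handling at month 6.

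The consequence is confined to exploratory aim 1, where it is partly offset by the T2 documentation, the hospital dates and the later SURF. The S-STS-based primary analyses and the 208 patients are untouched. The number affected cannot be derived from the document. The 4% to 18% (month 3) and 0% to 3% (month 6) depend entirely on the assumed stay distribution and on sites applying the rule literally. The change is cheap enough to be worth making.

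**What to change.** 1. Add a footnote to Table 1: when T2 falls within 2 weeks of month 3 or month 6, the skipped visit's SURF, and at month 6 the M.I.N.I., is completed at the merged contact. Mark both as conditional in the T2 column.
2. When T2 precedes month 6 by less than 2 weeks, keep a short month-6 contact for the S-STS and SURF, so that the 6-month observation period is complete.
3. Reconcile the Trial design sentence on T2 coinciding with T4 with the T3 and T4 column headings, so that all sites handle a combined visit in the same way.

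The cost is one footnote, a conditional form in the electronic CRF, and one additional existing form or a short contact for a few patients. No new instrument is needed.
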